**Methods:**

This non-randomized matched controlled study will utilize 28 male volleyball players aged between 18 and 25 years. Following baseline assessment, participants will be allocated to experimental group (INMT along with volleyball training) and control group (volleyball training along with a structured resistance training program) using non-randomized allocation procedure and a set of predefined criteria. The intervention will last 8 weeks, with three sessions per week. Primary outcome parameters such as body composition, anthropometric profiles, landing kinematics will be assessed using bioelectrical impedance analysis and landing error scoring system. The secondary outcome, vertical jump height, will be analyzed using vertec jump tester respectively. Group × time interaction test will be computed using ANCOVA, adjusted for baseline/linear mixed-effects model. Secondary outcome *p*-values will be adjusted for multiplicity, using the Holm-Bonferroni method.

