## Methodology

### Study design & ethical approval

This study will utilize a non-randomized matched controlled study approach to assess the impact of an eight-week integrated neuromuscular training (INMT) program on the anthropometric profile, jump-landing mechanics, and vertical jump height of young male volleyball athletes. Given the non-randomized matched controlled study, causal interpretation will be limited. Matching and baseline adjustment procedures will be used to reduce, but not eliminate, potential selection bias. However, certain methodological measures will be implemented to augment internal validity and to minimize bias. The participants baseline characteristics will be assessed to establish group comparability and minimize the confounding emerges from assessed variables. In addition, to reduce bias in the observation and measurement, the assessor who measured the outcome parameters will be blinded during the grouping and data collection phase (25). Participants will be divided into two groups: an Experimental Group (EG) that will receive INMT thrice a week for eight weeks, and a Control Group (CG) that maintain their standard volleyball training regimen. Despite the absence of random allocation, both groups will be comparable in baseline parameters such as age, height, weight, and body mass index (BMI). Purposive sampling will be utilized to enlist experienced volleyball players who satisfied certain inclusion criteria, guaranteeing adequate baseline proficiency and conditioning for the intervention.

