This study will adopt a matched controlled allocation approach to facilitate the matching between the groups. When random allocation is not feasible, non-random grouping with a matching baseline characteristic can be employed as it is well established method to compare groups (26). Participants will be matched based on the key baseline data such as such as age, gender, training periods, training duration and frequency, playing position, competitive level to maintain the uniformity as these factors will be perceived as potential confounders that may affect the result and balancing performance. Matching will be carried out prior to group allocation by pairing participants with identical baseline characteristics to guarantee the balance between the groups. Group allocation will be based on club accessibility and training logistics rather than random selection. Subsequently, after allocation, baseline homogeneity will be assessed using ANCOVA or Friedman test for continuous variable based on distribution of data and chi-square test for categorical variables. The standardized mean difference will be computed to examine the extent of any remaining baseline imbalance. If significant baseline difference exists after matching the appropriate variable will be included as covariates in the primary analyses to minimize the residual confounding. To mitigate expectation effects, the outcome assessor will be blinded to the group allocation, and the statistical analyses will be employed using data coding procedure to explicit the exposure of group allocation.

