The study will be conducted at private volleyball clubs located in Nilai and Subang, Malaysia. Ethical approval has been obtained from the University Research and Ethics Panel with ref. no. INTI-IU/FHLS-RC/BPHTI/1NY12025/007 and adhered to the declaration of Helsinki. This non-randomized matched controlled study has been registered with ClinicalTrials.gov (NCT07485348). The exercise intervention will be delivered by a sports physiotherapist who had over 10 years of experience in the relevant field. All participants will be briefed about the study's objectives and procedures. The participation of the subjects in this study will be voluntary, and each participant would be expected to sign the informed consent form before participation. Subjects will be allowed to discontinue from the study if they experience any form of musculoskeletal injury or any adverse effects observed during the delivery of the intervention. Any form of harm during the session will be documented through observation and self-reporting measures.

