## Discussion

The current non-randomized matched controlled study protocol is to create an efficient eight-week integrated neuromuscular training program that tends to enhance volleyball players’ anthropometric, body composition profiles, landing mechanics and vertical jump height. Although earlier studies have examined the association between anthropometric profiles, landing mechanics, jump height and performance metrics in volleyball, majority have investigated these variables in isolation rather than as interconnected elements of athletic performance (36). While previous study analyzed jump-landing mechanics under various conditions such as ball position, joint loading and screening reliability, associated with volleyball spike did not test the influence of anthropometric variable on this landing mechanics, nor guided to the most suitable intervention to control these covariates (37, 38). Moreover, there is a paucity in research that concurrently addresses changes in anthropometric variables, body composition, landing kinematics and performance after systematic INMT regimen. Therefore, the present study protocol aims to address this gap by evaluating the effects of an 8-week integrated neuromuscular training program on anthropometric, body composition variables, vertical jump height and jump-landing mechanics in male volleyball athletes.

Moreover, this study planned to utilize non-randomized matched controlled study design because of practical constraints encountered in team sports settings in terms of preserving team cohesion and existing training schedules (39). Participants will be matched based on key baseline characteristics, including age, sex, playing experience, and baseline performance measures, before group allocation. This matching procedure is intended to ensure that the study groups are comparable at baseline and to minimize potential selection bias resulting from differences in participant characteristics. Consequently, any observed differences in outcomes are more likely to be attributable to the intervention rather than pre-existing group differences. Furthermore, Lam et al. recommended that the intervention can be implemented within the participants’ routine training environment to enhance the ecological validity of the study and to increase the applicability of the findings to real-world sports practice (40).

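### Purposive enrolment plus allocation by club and logistics makes the arm likely foreseeable at entry, so testing baseline first does not protect against selective enrolment

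*Protocol article*

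**What the plan says.** The Abstract (Methods) puts testing first: "Following baseline assessment, participants will be allocated to experimental group". The section Study design & ethical approval adds that pairing also comes before allocation: "Matching will be carried out prior to group allocation by pairing participants with identical baseline characteristics to guarantee the balance between the groups".

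The same section gives the sampling method, "Purposive sampling will be utilized to enlist experienced volleyball players who satisfied certain inclusion criteria", and the basis of allocation: "Group allocation will be based on club accessibility and training logistics rather than random selection". It also names the setting: "The study will be conducted at private volleyball clubs located in Nilai and Subang, Malaysia". The Discussion explains the lack of randomization by "practical constraints encountered in team sports settings in terms of preserving team cohesion and existing training schedules".

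Two statements bear on bias. Blinding is described for the person measuring outcomes: "the assessor who measured the outcome parameters will be blinded during the grouping and data collection phase". Residual bias is admitted: "Matching and baseline adjustment procedures will be used to reduce, but not eliminate, potential selection bias". The Discussion nevertheless concludes that matching makes it more likely that differences in outcome come from the intervention than from differences already present.

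**The concern.** A sequence of baseline, pairing and then allocation suggests that entry and baseline data cannot be influenced by the coming arm. That holds only if the arm cannot be predicted. Here its determinants are properties of the club and its timetable, which exist before recruitment. Purposive sampling gives the recruiter discretion at exactly this point, and consent gives the player the same discretion.

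If keen or trainable players are approached more readily for one programme, or if players accept or decline according to the programme they expect, the arms differ in expected 8-week gain before training starts. Matching and baseline adjustment work on recorded variables. Motivation and expected response are not among them, so the difference would be counted as an effect of INMT. No later analysis can recover it.

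**Working it through.** **Can the arm be foreseen?** The protocol gives no figure on this, so the passages are set side by side.

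1. Determinants of the arm: club access and training logistics (Study design & ethical approval). Both are known before any approach.
2. Unit: pairing is described for individuals, but sites are private clubs and the Discussion wants teams and schedules left undisturbed. Allocation by club or team is the natural inference, though it is not stated. If a club were split, logistics would still be known beforehand.
3. Discretion: purposive sampling, then voluntary consent after a briefing.
4. Safeguards: the assessor is blinded and the analysis coded (Study design & ethical approval); verbal instructions are uniform (Jump height). These cover measurement and analysis. The article describes nothing that hides the coming arm from those who select, approach, consent or pair players.
5. Matching variables: age, sex, training history, position and competitive level in the design section; playing experience and baseline performance in the Discussion. None captures motivation.

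**How large could it be?** The documents give no size. Assume that selective entry adds s = 0.2 to 0.4 SD to the expected gain in one arm. The share of the planned effect depends on what f = 0.25 means (Sample size and participants).

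- *Two-group, two-time interaction.* The noncentrality is f² × N × 2/(1 − r). In terms of a between-group difference in change D (in outcome SDs) it is D² × (N/4)/[2(1 − r)]. Equating the two gives D = 4f = 1.0 SD. The share is 0.2/1.0 = 20% to 0.4/1.0 = 40%.
- *Baseline-adjusted contrast of two groups.* d = 2f = 0.5 SD. The share is 0.2/0.5 = 40% to 0.4/0.5 = 80%.

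**Which reading fits the stated 28 players?** Under the interaction reading with an assumed pre-post correlation r = 0.6, the noncentrality is 0.0625 × 28 × 2/0.4 = 8.75 and power is 0.813, so 28 is reproduced. The protocol does not state r; at r = 0.5 the same formula needs 34. Under the adjusted-contrast reading, f = 0.25 with one covariate needs 128, and 28 players give power of about 0.25. The interaction reading, hence 20-40%, fits the stated N better. The text names both ANCOVA and a mixed model, so both ranges are shown.

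**Effect on the false-positive rate (illustration).** With 14 per arm, no true effect and an unadjusted two-sided 5% test, the noncentrality is s × √(14/2) = s × √7, where s is in SDs of the variable compared. An assumed shift of 0.2 SD gives rejection in 8% of trials; 0.3 SD gives 12%.

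**The case against.** The design is openly non-randomized. It says that causal interpretation is limited, admits residual selection bias and never claims concealment. That stands: the bias is not undisclosed. But the admission is general and sits beside a promise of guaranteed balance and a statement favouring attribution to the intervention. Neither is supported when entry is unprotected.

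A reader might infer four stronger things that the documents do not support:

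- *Each club goes wholly to one arm, so the arm is certain in advance.* The protocol states neither this nor when the arm is fixed. Likely foreseeability is as far as the text goes.
- *Baseline testers know the arm and test differently.* The protocol blinds the assessor and prescribes uniform instructions. One may doubt that blinding survives allocation by club, but the point does not need this. Low effort at baseline is also a narrow route: body composition and anthropometry do not depend on effort, and jump height, the clearest effort test, is secondary.
- *Consent reveals the arm.* Consent pages are not shown, and an article may leave invitation details to the full protocol. The point rests on what the article itself fixes: sampling method, allocation basis and order.
- *Most of the planned effect could be selection.* The 40-80% range needs the reading of f that does not reproduce 28 players, and the shift itself is assumed.

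It is also fair to object that delaying the announcement conceals little if logistics already determine the arm. That stands, and the fix needs a fallback.

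**Conclusion.** The concern holds in limited form. Purposive choice of players, combined with allocation on facts known before approach, leaves enrolment open to selection on unmeasured traits. The stated order and the pairing do not prevent it, and assessor blinding does not reach it.

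This rests on one inference: that club and logistics let recruiters and players predict the arm. The size is unknown. Under an assumed 0.2 to 0.4 SD shift it is 20-40% of the planned effect on the interaction reading and 40-80% on the adjusted-contrast reading. The change should be made before enrolment, but the point does not invalidate a design that disclaims randomization.

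**What to change.** In Study design & ethical approval, and in the Abstract where the order is given:

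1. Replace purposive choice within a club by inviting every eligible player, or consecutive eligible players up to the recruitment target of 31.
2. Use one invitation and consent wording that describes both programmes without saying which the club will receive.
3. Complete and lock baseline testing at all clubs before the programme for each club is decided and announced.
4. Report eligible, approached, declined and enrolled players by club.

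Non-random allocation can stay. The cost is a short delay at the first club until the last has finished baseline, plus wording and a recruitment log.

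If logistics already settle which club gets which programme, steps 1 to 3 conceal only in part. The protocol should then say plainly that allocation is not concealed, state when each club's programme was fixed, and soften both the guarantee of balance in the design section and the attribution sentence in the Discussion. That costs only wording.

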### Sample size and participants

The target population will be comprised of male volleyball players aged 18 to 25 years, with a minimum of one year of continuous playing experience at university level, playing position setter, hitter, blocker, a training frequency of at least twice per week with minimum weekly training volume of 3 h, previous lower limb injury status will be collected. Individuals who had sustained a recent lower-limb injury or undergone surgery within the past six months, individuals with neurological or vestibular diseases, or participants involved in other structured training programs will be excluded. This selection guaranteed a uniform athletic background among participants. LESS, anthropometric measures, and body composition will be considered as primary outcomes, and vertical jump height will remain as a secondary outcome. Sample size has been calculated using G*Power (version 3.1.9.4) based on effect sizes obtained from research conducted by Pfile et al., which demonstrated a significant change in LESS after 6 weeks of NMT (F^2^, ^10^ = 6.29, *p* = 0.009) providing a partial eta square (*η*^2^p) of 0.557 and cohen's f of 1.12 (27). However, this study utilized single-group repeated measures instead of a controlled trial, and a more cautious interaction effect size (f = 0.25) was computed using ANCOVA, adjusted for baseline/linear mixed-effects model. Secondary outcome *p*-values will be adjusted for multiplicity, using the Holm-Bonferroni method with a significance level of *α* = 0.05 and statistical power of 0.8, which necessitated a minimum of 28 participants (14 per group). The total recruiting target will be established at 31 athletes to account for a probable 10% dropout. This sample size calculation has been performed considering the primary outcome only; results regarding secondary outcomes should be considered exploratory.

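### The two matching lists disagree, and pairing on identical characteristics, said to guarantee balance, is almost certainly unattainable with about 31 players

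*Protocol article*

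**What the plan says.** In the protocol article, *Study design & ethical approval* says that participants are "matched based on the key baseline data such as such as age, gender, training periods, training duration and frequency, playing position, competitive level". Matching precedes allocation and works by "pairing participants with identical baseline characteristics to guarantee the balance between the groups". Groups are then formed by club: "Group allocation will be based on club accessibility and training logistics rather than random selection". The sites are "private volleyball clubs located in Nilai and Subang, Malaysia".

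The *Discussion* describes the matching differently: "Participants will be matched based on key baseline characteristics, including age, sex, playing experience, and baseline performance measures, before group allocation". It goes on to say that outcome differences are therefore more likely to be due to the intervention than to pre-existing differences.

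The design section also contains softer statements. Causal interpretation is to be limited, and matching with baseline adjustment is expected to lessen selection bias without removing it. Standardised mean differences will be computed, and a variable becomes a covariate if a significant baseline difference remains.

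*Sample size and participants* requires men aged 18 to 25 who play as setter, hitter or blocker. It sets only minimum values for experience and training, needs 14 players per group, and recruits 31.

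**The concern.** Without randomisation, matching is the main protection at the design stage against groups that differ before training starts. Two things undermine it as written.

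- **The variables are not settled.** Whether baseline performance is matched matters a great deal when the outcomes are LESS and jump height, and the two sections answer differently. They also differ on position and training load.
- **The rule cannot realistically be followed.** If most players have no identical partner, they must be left out or paired more loosely, and the article does not say which. The guarantee of balance, and the attribution claim in the *Discussion*, would then rest on matching that was not done as described.

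**Working it through.** **1. The two lists side by side**

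| Variable | Design section | Discussion |
|---|---|---|
| Age | yes | yes |
| Sex/gender | yes (constant) | yes (constant) |
| Training periods / playing experience | training periods | playing experience (may overlap) |
| Training duration and frequency | yes | no |
| Playing position | yes | no |
| Competitive level | yes | no |
| Baseline performance | no | yes |

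Of the variables that can separate players, only age is clearly on both lists.

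**2. The pool**

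The recruiting target reproduces: 28 × 1.10 = 30.8, rounded up to 31. At most 15 pairs are possible.

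**3. Expected number of identical pairs**

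Inputs from the article: 31 players, 8 whole-year ages (18 to 25) and 3 positions. Assumed, because the article gives no distributions or category widths: the number of levels of every other factor, and that all factors are uniform and independent.

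With K equally likely combinations (cells), the chance that a cell holds an odd number of players is P(odd) = [1 − (1 − 2/K)^31]/2. Each such cell leaves one player unpaired, so

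expected pairs = [31 − K × P(odd)]/2.

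For age × position, K = 8 × 3 = 24:
- (1 − 2/24)^31 = 0.0674
- P(odd) = 0.4663
- 24 × 0.4663 = 11.19
- expected pairs = (31 − 11.19)/2 = 9.9

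| Factors matched | K | Expected pairs |
|---|---|---|
| Two age bands × position | 6 | 14.0 |
| Whole-year age × position | 24 | 9.9 |
| + frequency (2 levels) | 48 | 6.7 |
| Age × position × frequency (3) × competitive level (2) | 144 | 2.8 |
| Age × position × frequency (3) × experience (4) | 288 | 1.5 |
| Age × position × frequency (3) × duration (3) × experience (3) × level (2) | 1,296 | 0.35 |

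Simulation gives the same averages. A more favourable, non-uniform case has bunched ages, frequency and experience each split 70/30, and competitive level constant. It gives 6.3 pairs.

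**4. Pairs that can straddle the clubs**

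If club fixes the group, a pair helps balance only when its members are in different groups. Simulating 31 players already split 15 and 16 lowers the averages to 6.0 (24 cells), 3.8 (48 cells) and 1.6 (144 cells). For the 6-cell case the average falls from 14.0 to 10.7.

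**5. Whether the fallback repairs it**

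Covariates are added only after a significant baseline difference. I use a two-sided 5% t-test with 14 per group as a stand-in for the baseline test. The observed difference must exceed 2.056 × √(2/14) = 0.78 SD to be significant. Power is 0.25 for a true standardised difference of 0.5 and 0.53 for 0.8. Imbalances of that size would trigger adjustment about a quarter and about half of the time.

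**The case against.** The strongest reply has four parts.

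- **Both lists are open-ended.** They are introduced as examples, and the *Discussion* is a summary. This stands in part: the lists are inconsistent, not mutually exclusive. Open-endedness does not settle which variables are used, though.
- **The pair counts depend on assumptions.** A reader might infer that 14 pairs are required and cannot be formed. The article asks for 14 per group, never 14 pairs, and describes no pair-based analysis. Two age bands with position alone would give 14 or more pairs in about 82% of simulations if club is ignored. So impossibility is not shown. But that case drops most of the listed factors and is not identity.
- **The article already hedges.** It says matching will not remove selection bias, and it plans standardised differences, baseline-adjusted analysis and extra covariates. This is a real mitigation, so one cannot conclude that the groups will be unbalanced. But the hedge contradicts the guarantee, and the covariate trigger is weak at this sample size.
- **Calipers are detail for a fuller document.** That is fair, and their absence alone would be no finding. The point is that the article does state a rule, and the rule is not workable.

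Three further inferences are not supported. Height, weight and BMI are named as characteristics on which the groups will be comparable, not as matching variables, so they are not a third conflicting list. Eligibility sets a minimum of university-level experience and does not fix competitive level, so that variable need not be dropped. An odd target of 31 need leave only one player over, which is trivial when dropout is expected.

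**Conclusion.** The concern holds in limited form. The design section and the *Discussion* disagree on whether baseline performance, playing position, training duration and frequency, and competitive level are matched. This rests on the text alone.

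The rule of identical pairing is almost certainly unattainable with about 31 players. Assuming uniform, independent factors, it yields about 10 pairs on whole-year age and position, and about 1.5 to 7 with one or two further factors. Coarse banding would raise these counts, and requiring pairs to straddle the clubs would lower them. The guarantee of balance is therefore unsupported and conflicts with the article's own statement that selection bias will remain. What is shown is that the balance claim lacks a workable procedure, not that the groups will in fact differ.

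**What to change.** 1. State one closed list of matching variables, the same in the design section and the *Discussion*. Omit sex. Keep competitive level if it varies among recruits. Include a baseline performance measure that is available before allocation. Vertec jump height is read at testing. Baseline LESS qualifies only if the videos are scored by then, and *Landing mechanics* says they are assessed later.
2. Replace identical pairing with stated bands or calipers in a priority order.
3. Require the two members of each pair to fall in different groups, and say how this works under club-based allocation. Without it, no caliper can balance the arms.
4. State that players without a partner stay in the analysis.
5. Adjust for the matching variables that matter most, either by pre-specification or by a stated standardised-difference threshold, instead of only after a significant baseline test.
6. Replace the guarantee of balance, and the attribution claim in the *Discussion*, with a statement that matching reduces imbalance. Report the achieved standardised differences.

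The cost is mostly wording, because baseline assessment already precedes allocation. The downsides are a weaker balance claim and possibly earlier scoring of the baseline videos.

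### Confounders other than the baseline outcome enter the primary model only if a baseline significance test flags them, and with 14 per group that test misses sizeable imbalances

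*Protocol article*

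**What the plan says.** All of the following is in the protocol article.

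- **Allocation** (Study design & ethical approval): "Group allocation will be based on club accessibility and training logistics rather than random selection".
- **Confounders** (same section): players are matched on age, gender, training periods, training duration and frequency, playing position and competitive level, because "these factors will be perceived as potential confounders that may affect the result and balancing performance".
- **Baseline check** (same section): "baseline homogeneity will be assessed using ANCOVA or Friedman test for continuous variable based on distribution of data and chi-square test for categorical variables".
- **SMD** (same section): "The standardized mean difference will be computed to examine the extent of any remaining baseline imbalance". No threshold is given and no action follows from it.
- **Covariate rule** (same section): "If significant baseline difference exists after matching the appropriate variable will be included as covariates in the primary analyses".
- **Primary model** (Data analysis): a group-by-time test by ANCOVA adjusted for baseline, or a linear mixed model. No matching variable, pair or club term is named. Age and BMI appear only in the imputation model.
- **Matching, second description** (Discussion): players are matched on key characteristics, "including age, sex, playing experience, and baseline performance measures, before group allocation".

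**The concern.** In a non-randomised comparison, matching and adjustment are the only protection against confounding, and the article relies on both. How much a variable confounds depends on the size of its imbalance and its link with the outcome. A p-value measures neither, and in a small study it is mostly a statement about sample size. Under the stated rule, a variable that the article itself calls a potential confounder is left out whenever a weak test fails to reach significance. The SMD, which does measure the imbalance, is ignored at that step.

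Two further problems follow. The covariate set is unknown until the data are seen. And the test that decides it is poorly chosen, so two analysts could apply the rule differently. At stake is bias in the group effect from differences between clubs in age, training or level.

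**Working it through.** **Inputs.** 14 per group, 28 in total, and a recruiting target of 31 (Sample size and participants). No alpha is given for the baseline tests; two-sided 0.05 is assumed. The plan states no detection limit of its own, so there is no figure to reproduce first.

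**1. Smallest observed difference that reaches significance, unpaired t-test.**
t(0.975, n1+n2−2) × √(1/n1 + 1/n2)
- 14 v 14: 2.056 × √(2/14) = 0.777 SD
- 15 v 16 (all 31 recruited and analysed): 0.735 SD

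**2. The same for a paired t-test on 14 pairs**, within-pair correlation r: t(0.975, 13) × √(2(1−r)/14)
- r = 0: 0.82 SD
- r = 0.3: 0.68 SD
- r = 0.5: 0.58 SD
- r = 0.7: 0.45 SD

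**3. Chance that the unpaired test flags a true imbalance** (noncentral t, 26 df, noncentrality d × √7)
- d = 0.2: 8%
- d = 0.3: 12%
- d = 0.5: 25%
- d = 0.8: 53%
- d = 1.0: 72%

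**4. Friedman.** It ranks within related blocks, so it does not compare two independent groups. With 14 matched pairs as blocks it reduces to a sign test with statistic (2x − 14)²/14, where x is the number of pairs favouring one group.
- x = 10: 36/14 = 2.57, p = 0.109
- x = 11: 64/14 = 4.57, p = 0.033 (exact sign test p = 0.057)

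At least 11 of 14 pairs must therefore point the same way. With uncorrelated pairs this flags a true 0.5 SD imbalance about 20% of the time and 0.8 SD about 40%. With the exact p-value the figures are 7% and 19%.

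**5. Chi-square.** At 14 per group the uncorrected test needs a difference of roughly 29 percentage points (0 v 4 of 14, p = 0.031) to 43 points (3 v 9 of 14, p = 0.022).

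**6. Bias left by the rule.** The inputs here are assumptions, not figures from the article: zero true effect, one covariate with a true 0.5 SD imbalance, residual SD 0.7, baseline outcome always in the model, unpaired t-test as the gate. Simulated with 6,000 runs:
- coefficient 0.1: bias 0.03, false-positive rate 5.1%
- coefficient 0.2: bias 0.055, false-positive rate 4.7%
- coefficient 0.4: bias 0.10, mean standard error 0.31, false-positive rate 5.5%
- coefficient 0.4 with a paired test and pair correlation 0.7: bias 0.05, false-positive rate 4.6%

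A separate run of 10,000 at coefficient 0.4 selected the covariate in 24% of runs. Mean bias was 0.105 under the rule, 0.198 if never adjusted (expected 0.4 × 0.5 = 0.20) and 0.001 if always adjusted. The rule thus removes about half the bias. Relative to precision, 0.10/0.31 is about a third of a standard error.

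**7. Matching lists side by side.** Study design & ethical approval includes playing position and competitive level but not baseline performance. The Discussion includes baseline performance but not position or level. Both describe matching before allocation.

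**The case against.** Several stronger readings are tempting, and the article does not support them.

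- **That all adjustment hangs on the test.** It does not. Data analysis plans baseline adjustment whatever the tests show, and the baseline outcome is plausibly the strongest prognostic variable. The rule reaches only the other variables.
- **That confounders up to 0.78 SD always stay unadjusted.** That figure belongs to an unpaired t-test at an assumed alpha, and the article names neither. If matching works and the pairing is used, the limit is lower.
- **That none of the named tests suits two groups.** Chi-square does, though it is weak here. ANCOVA can compare two groups; the article simply names no covariate for this use. Friedman can be run on pairs, but only as a sign test.
- **That error rates are badly distorted.** In the runs above, false-positive rates stay between 4.6% and 5.5%. In the 10,000-run simulation, interval coverage was 94.6% under the rule against 95.1%. The bias also presumes a 0.5 SD imbalance that survives matching, and its absence under fixed adjustment holds by construction, because the only simulated confounder is the one adjusted for.
- **That there are three conflicting matching lists.** The sentence on age, height, weight and BMI in Study design & ethical approval expresses expected comparability and is not a matching list. The two real lists are introduced as examples, but that does not settle whether baseline performance is matched.

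The article also concedes that causal interpretation will be limited. What stands is that it states a rule, not merely an omission that an analysis plan might fill, and the rule bases adjustment on the wrong quantity.

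**Conclusion.** The point holds in limited form. For potential confounders other than the baseline outcome, entry to the primary model depends on a significance test with little power at 14 per group, while the SMD is left out of the decision. A true 0.5 SD imbalance would be missed about three times in four (unpaired, two-sided 0.05 assumed). Friedman is a poor choice for the check, and the ANCOVA check is not fully specified.

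The likely bias is modest: 0.03 to 0.10 outcome units for coefficients 0.1 to 0.4, up to about a third of a standard error, under the stated assumptions. It would be larger with a stronger confounder. The change should be made because the rule is unsound in a study allocated by club and the remedy is cheap, not because the primary result would otherwise be invalid.

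**What to change.** - Delete the significance rule and the ANCOVA/Friedman homogeneity tests.
- Keep the planned adjustment for the baseline outcome. Add a short covariate list fixed in advance from variables already collected and named as confounders, for example age and weekly training frequency, whatever the baseline p-values.
- Report SMDs descriptively. Pre-specify a sensitivity model that adds any variable above a stated SMD threshold, so that position, level and similar variables left off the short list are still examined.
- Give one matching list in Study design & ethical approval and the Discussion, and say whether baseline performance, playing position and competitive level are on it.

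**Cost:** wording changes, and two or three of roughly 25 residual degrees of freedom (28 players less intercept, group and baseline). The list must stay short at this sample size. **Limit:** if the groups follow clubs, no covariate adjustment can separate the treatment effect from the club effect, and the article should say so.
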